## Abstract

**Background:**

The need for cost-effective interventions for people suffering from major depressive disorders is essential. Behavioral activation is an intervention that can largely benefit from the use of new mobile technologies (for example smartphones). Therefore, developing smartphone-based behavioral activation interventions might be a way to develop cost-effective treatments for people suffering from major depressive disorders. The aim of this study will be to test the effects of a smartphone-delivered behavioral activation treatment.

**Methods:**

The study will be a randomized controlled trial with a sample size of 120 participants, with 60 patients in each group. The treatment group includes an 8-week smartphone-based behavioral activation intervention, with minimal therapist contact. The smartphone-based intervention consists of a web-based psychoeducation, and a smartphone application. There is also a back-end system where the therapist can see reports from the patients or activities being reported. In the attention control group, we will include brief online education and then recommend use of a smartphone application that is not directly aimed at depression (for example, ‘Effective meditation’). The duration of the control condition will also be 8 weeks. For ethical reasons we will give the participants in the control group access to the behavioral activation treatment following the 8-week treatment period.

**Discussions:**

We believe that this trial has at least three important implications. First, we believe that smartphones can be integrated even further into society and therefore may serve an important role in health care. Second, while behavioral activation is a psychological treatment approach for which there is empirical support, the use of a smartphone application could serve as the therapist’s prolonged arm into the daily life of the patient. Third, as we have been doing trials on guided Internet treatment for more than 10 years it is now time to move to the next generation of information technology - smartphones - which are not only relevant for Swedish conditions but also for developing countries in the world which are increasingly empowered by mobile phones with Internet connection.

**Trial registration:**

ClinicalTrials.gov NCT01463020

## Background

Major depression is expected to be the disorder with the highest disease burden in high-income countries by the year 2030 [1]. Estimated costs of depression are €177 million and €147 annually per 1 million inhabitants for major and minor depression, respectively [2]. Even if several effective psychological [3] and pharmacological treatments [4] are available for the treatment of depression, it has been shown that current treatment methods are only capable of reducing the burden of disease of depressive disorders with about one third [5]. Therefore, there is a need for cost-effective interventions that can be made available to a larger part of the population suffering from major depressive disorders. Furthermore, behavioral activation is an intervention that can largely benefit from the use of new mobile technologies (for example smartphones). One important feature of mobile technology is the possibility for the therapist to reach the patient between sessions and thus create direct incentives for behavioral activation in everyday life [6]. Therefore, developing smartphone-based behavioral activation interventions might be a way to develop a cost-effective treatment for people suffering from major depressive disorders. Another advantage with behavioral activation would be that it is more amenable to dissemination, especially via less experienced therapists and/or self-administration [7].

The efficacy of behavioral activation in the treatment of major depressive disorders has been established in a number of studies over the last four decades [8]. Furthermore, a dismantling study showed that behavioral activation can be as effective as the full cognitive behavioral therapy (CBT) treatment package [9]. In a later study, behavioral activation was found to be as effective as antidepressant medication [10], and more effective than cognitive therapy for more severely depressed patients. A series of reviews and meta-analyses also show that behavioral activation is at least as effective as full CBT packages that include both cognitive and behavioral components [11]. There are however somewhat different conceptualizations of behavioral activation, with the most recent versions covering behavioral avoidance [12]. However, all have activity scheduling as a treatment component [13]. More recent behavioral activation treatments have incorporated ingredients from Acceptance and Commitment Therapy (ACT), for example the role of values when defining treatment goals [14].

Boschen and Casey [6] summarized the advantages of using mobile phones in CBT, and the same advantages apply to smartphones: (1) mobile; (2) accepted in society in general; (3) relatively cheap (this also applies to smartphones which on average tend to be less expensive than computers); (4) they are a device with comparatively low ongoing maintenance costs; (5) they are a device already owned by a large number of people; (6) they are almost always on in that they continue to operate; (7) they are almost always connected; (8) they are programmable, meaning they are able to run novel applications software; (9) they are capable of recording media, including audio, photographs, and in many cases video, as well as being able to play or show these media to the user; (10) they are capable of interacting with the user to allow input of data using a keypad, keyboard, or touch screen; and (11) they are generally designed to be easy to use for most of the population. Moreover, mobile phones can be integrated into CBT homework, as their use attracts no attention, allowing users to interact with a handset without fear of stigma or judgment.

It is now well established that guided self-help treatment can be as effective as face-to-face psychotherapy for mild to moderate depressive symptoms [15]. Also, the treatment effects seem to persist during long-term follow-up [16]. There are, however, to our knowledge no controlled trial on Internet-delivered pure behavioral activation and no study using smartphones.

### Trial objectives and purpose

The aim of this study will be to test the effects of a smartphone-delivered behavioral activation treatment. The study is based on our previous work on guided Internet-treatment for depression [17], but in this study the treatment content will be delivered via smartphone, using a recently developed smartphone application. As waiting-list control groups are regarded as unsuitable to test the effects of treatments, we plan to have a non-specific smartphone application not dealing with depression or behavioral activation. This will probably be the first controlled study on smartphone delivered depression treatment and therefore we will begin by conducting an efficacy study [18], with participants recruited via mass media and the Internet. We expect the smartphone application to be superior to the control condition.

## Methods/design

The current study will be a randomized controlled trial with a sample size of 120 participants. The study protocol was approved by the regional Ethics Review Board in Linköping, Sweden. The protocol was approved by [name] and the reference number is Dnr: 2011/395-31. Written informed consent was obtained from all participants after the procedure had been fully explained.

### The intervention

An 8-week smartphone-based behavioral activation intervention with minimal therapist contact has been developed by our group. The intervention is based on our previous experiences with Internet-based depression treatment [15,16,19-23]. The smartphone-based intervention consists of a web-based psychoeducation, and a smartphone application. There is also a back-end system where the therapist can see reports from the patients or activities being reported. The concept of the intervention was built with the intention to target some of the aspects of current Internet-delivered interventions that could be improved. Although the Internet is effectively used for distributing psychological treatment programs to improve mental health [24-26], including treatment of mild to moderate major depression [27], it has been argued that Internet-based treatment applications have limitations [28,29]. One important limitation is the lack of assimilation into the user’s daily life, which is a crucial aspect of behavioral activation treatments for depression [12]. Even if paper versions of text material can be used and contact with the therapist can be handled via the Internet, these two options may not be practically feasible. Mobile phones, on the other hand, are often ubiquitous and are hence present when behaviors occur. Nowadays, access to the Internet can be facilitated by means of smartphones. Another limitation of Internet-based treatments for depression, delivered via computers, is that they tend to be text-based, often reaching close to 200 pages of reading [20]. Smartphone applications tend to be more user-friendly and condensed than regular web pages (for example the difference between a smartphone application for a newspaper and web pages for the same newspaper), which could be an attractive feature for persons with depression who easily feel fatigued and need encouragement to work through the program [30]. The latter aspect is important, as guidance appear to be crucial to prevent drop-out from guided self-help treatments [31], which was recently confirmed in a meta-analysis [15]. Finally, a challenge for modern depression treatments is to integrate information technology in the regular treatment [29]. In other words face-to-face treatments could benefit from using smartphones as an adjunct to the regular sessions, which in the case of behavioral activation treatments for depression could facilitate activity scheduling and homework, which are crucial elements of the treatment. It may also be possible to reduce the number of sessions.

A prototype of the smartphone application, together with a psychoeducation, has been tested in a pilot study ([name], [name], [name]: Development and initial evaluation of a smartphone application based on acceptance and commitment therapy, unpublished). This prototype was however not directed at depression. The results from the pilot study gave us useful information and we concluded that the intervention include some important features that could be further developed and tested. The results also showed that the smartphone application was used by some participants in situations where it was difficult to use a computer connected to the Internet, for example in the underground train, on the bus and train, and so on. More generally, this might carry implications that the platform of mobile phones does not only assimilate an intervention into a user’s daily life, but also increases the awareness of the intervention, and thus can increase adherence to the intervention. In light of these observations we believe it is feasible to proceed and test if behavioral activation can be presented in the format of a smartphone application.

### Attention control

In the attention control group, we will include brief online education and then recommend use of a smartphone application that is not directly aimed at depression (for example, ‘Effective meditation’). The duration of the control condition will also be 8 weeks. For ethical reasons we will give the participants in the control group access to the behavioral activation treatment following the 8 week treatment period.

### Sample size

We will include a total of 120 individuals. With 60 patients in each group, an effect size of Cohen’s *d* = 0.60 will be statistically significant (80% power, 5% level), which we will view as a clinically relevant difference between the two conditions.

### Referral and recruitment

Patients will be recruited via advertisement in newspapers, other media, and the Internet. Only persons who already use smartphones will be invited to participate.

### Inclusion criteria

We will include participants with an ongoing primary diagnosis of major depression of mild to moderate character. Diagnoses will be made over the telephone using the Mini-International Neuropsychiatric Interview (MINI) [32]. To administer clinical interviews via telephone has shown to give the same result as doing it face-to-face [33,34]. Medication will be allowed with the requirement that the dose is stable. Consenting participants need to be fluent in Swedish and have access to the Internet as well as a smartphone.

### Exclusion criteria

Persons with suicidal intent and patients for whom the depression is directly linked to another major primary psychiatric disorder (for example, psychosis or bipolar disorder) will be excluded and referred to other treatment resources. In addition, people with a history of misuse of alcohol or drugs will be excluded.

### Informed consent

Participation will require a written informed consent.

### Withdrawal

Participants can at any time withdraw from the treatment or the study without specifying the reason.

### Safety monitoring and reporting

We will adhere to the Swedish Personal Data Act. No sensitive data will be saved on a computer in which the person providing data can be identified. All Internet and smartphone activities will be highly secure, with encrypted information as well as no contact outside of a closed contact system. If participants decline further participation, the data will be removed.

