
### Moderators and mediators

As secondary outcome we will include the Beck Anxiety Inventory (BAI) [42], the Quality of Life Inventory (QOLI) [43] and Acceptance and Action Questionnaire (AAQ-II) [44]. The BAI is a 21-item self-report inventory for measuring the severity of anxiety in psychiatric populations [42]. De Beurs *et al.*[45] showed that the BAI has high internal consistency in panic patients (Cronbach’s a = 0.92) and good test-retest reliability (0.83). The QOLI consists of 16 areas rated by the subject concerning importance and satisfaction. The instrument’s internal consistency is high, between a = 0.77 and 0.89, and the 1 month test-retest reliability lies between r = 0.80 and 0.91 [43]. The AAQ-II is a 10-item, 7-point Likert scale that assesses psychological flexibility - a term for the ability to accept unwanted internal experiences and engage in valued actions. The AAQ II has shown good reliability (test-retest reliability = 0.81–0.87) and validity [44].

Other measures will be included as potential predictors of outcome such as education, number of previous episodes, and so on. Finally, we will include the Trimbos and Institute of Medical Technology Assessment Cost Questionnaire for Psychiatry (TIC-P [46]), which is a questionnaire designed to measure health related costs. Cost-effectiveness studies also often involved a measure called the EQ-5D [47]. The study will follow the guidelines given in the CONSORT statement [48,49], with the exception of double-blinding, which is not possible in psychotherapy studies. Other features such as intention-to-treat (mixed models approach [50]) and statistical power calculations will be adhered to. The theoretical rationale for smartphone supported behavioral activation is the observation that activity is related to depressive symptoms [8] and that behavioral change may be facilitated by the increased adherence provided by the smartphone.

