### Statistical analysis

An intention-to-treat design will be used when analyzing post-treatment data and data collected at 1-year follow-up. Between-group changes at post-treatment and at 1-year follow-up will be calculated using analyses of covariance (ANCOVAs), with pre-treatment scores as the covariate. Effect sizes between and within the two groups will be calculated with Cohen’s d computed with the pooled standard deviation.

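### Read literally, the data-removal rule takes randomised participants' collected scores out of the promised intention-to-treat analysis; the number affected and the bias cannot be known from the article

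*Protocol article*

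**What the plan says.** Four statements in the protocol article bear on this point.

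- **Withdrawal:** "Participants can at any time withdraw from the treatment or the study without specifying the reason". Leaving treatment and leaving the study are named as two different things.
- **Safety monitoring and reporting:** "If participants decline further participation, the data will be removed". This closes a paragraph on the Swedish Personal Data Act, identifiability and encryption. It does not say which of the two kinds of withdrawal it means.
- **Statistical analysis:** "An intention-to-treat design will be used when analyzing post-treatment data and data collected at 1-year follow-up". The between-group comparisons are "calculated using analyses of covariance (ANCOVAs), with pre-treatment scores as the covariate".
- **Moderators and mediators:** "Other features such as intention-to-treat (mixed models approach [50]) and statistical power calculations will be adhered to", and "The study will follow the guidelines given in the CONSORT statement [48,49], with the exception of double-blinding".

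No section says how a randomised participant whose data were removed stays in the analysis, and none overrides the removal rule.

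**The concern.** An intention-to-treat analysis compares the groups as randomised. The removal rule is triggered by something that happens after randomisation, and the decision to leave may be related to arm and to how the person is doing. If it is, the groups analysed are no longer the groups randomised.

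Removal also differs from ordinary dropout. A participant who merely fails to return a questionnaire still has a baseline record, and perhaps later scores, that a model or an imputation can use. A participant whose record is removed has nothing left for either the mixed model or the baseline-adjusted ANCOVA. No later analysis plan can repair this, because the data no longer exist. With 1-year and 2-year follow-ups planned (Outcome measures), there is a long period in which someone can decline to continue after giving a valid week-8 score.

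**Working it through.** **1. What the text covers.** The rule speaks of declining *further* participation, so it applies to people already in the study, randomised participants included. The trigger is the declining itself, not a request for erasure. What is removed is simply the data, without qualification.

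**2. Whom it would affect.** Three kinds of participant have to be kept apart.

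| Participant | Outcome score without the rule | Effect of the rule |
|---|---|---|
| A. Leaves the study before week 8 and gives no week-8 score | Missing anyway | Baseline lost as well |
| B. Gives a week-8 score, later declines the 1-year follow-up | Available | A collected primary outcome is erased |
| C. Stops treatment but stays in the study | Could be collected | Removed only if stopping treatment counts as declining participation, which the text leaves open |

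For B the clash with intention-to-treat is direct. If removal comes before the post-treatment analysis is closed, the primary comparison changes. If it comes later, the 1-year analysis and any reanalysis use a different set from the one already reported.

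**3. The plan's nearest figure.** The article plans 120 participants, 60 per group (Sample size; Abstract), and expects about 30% not to complete post-treatment measures, leaving 84 (Outcome measures). This reproduces: 120 × (1 − 0.30) = 84. It counts non-completers. It is not a forecast of deletions, and the article gives none.

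**4. Size under assumed rates.** The inputs here are assumptions. Let a fraction w of an arm be removed according to a latent score correlated ρ with the outcome (1 SD units). The mean of those kept shifts by ρ·φ(c)/(1 − w), where c is the (1 − w) quantile of the standard normal. Take ρ = 0.5:

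- w = 0.10: c = 1.282, φ(c) = 0.1755, shift = 0.5 × 0.1755 / 0.90 = 0.097
- w = 0.05: c = 1.645, φ(c) = 0.1031, shift = 0.5 × 0.1031 / 0.95 = 0.054
- Spurious difference for 10% v 5%: 0.097 − 0.054 = 0.043 SD

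With no true effect:

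| Removed, one arm v the other | ρ = 0 | ρ = 0.3 | ρ = 0.5 |
|---|---|---|---|
| 10% v 5% | 0 | 0.03 | 0.04 |
| 20% v 10% | 0 | 0.05 | 0.08 |
| 30% v 10% | 0 | 0.09 | 0.15 |
| equal | 0 | 0 | 0 |

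Precision matters less. Removing 5% to 30% of 120 takes out 6 to 36 people. Power for d = 0.60 (two-sided 5%, t-test) falls from 90.3% at 60 per group to between 88.8% and 77.6%.

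**5. A stronger scenario, and how far it depends on its assumptions.** Let the log-odds of removal rise by 1 per SD of worse outcome. The true d is 0.30, and the active arm loses 10%, 20% or 30%.

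| Scenario | 10% | 20% | 30% |
|---|---|---|---|
| Active arm only, control loss random, no baseline adjustment | 0.39 | 0.47 | 0.55 |
| Same, with ANCOVA, assumed pre-post correlation 0.5 | 0.37 | 0.43 | 0.49 |
| Same, but leavers' baselines kept and no week-8 score exists | 0.37 | 0.43 | 0.50 |
| Same removal model in both arms, no baseline adjustment | 0.28 | 0.26 | 0.26 |

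The first row is an upper illustration, not an estimate. The second and third rows are essentially equal. For people in group A the bias comes from outcome-dependent missingness and would be there without the rule. What the rule itself adds comes mainly from outcome scores that were collected and then erased (group B). The last row shows that even the direction is not fixed.

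**The case against.** The strongest reply is that the sentence belongs to a data-protection paragraph. It may mean only erasure when consent to data use is withdrawn, or removal of identifying details. The article supports a milder reading elsewhere: it distinguishes leaving treatment from leaving the study, handles missed post-treatment measures separately as dropout, and expects all patients to be interviewed again after treatment. If few people decline, little is lost.

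Much of this stands. A reader might infer that anyone who stops using the application or skips a questionnaire is deleted. The text does not establish that. Nor does it support reading the 30% as a deletion rate, or concluding that the treatment effect will be inflated by a particular amount. A reader might also infer that people who worsen vanish from a harms record, but the article describes no such record, so the point has no footing.

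What does not stand is the suggestion that the milder reading removes the conflict. The sentence contains none of those limits, and a data manager following it literally would remove collected outcomes from randomised people.

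**Conclusion.** The point holds in a limited form. The removal rule as worded conflicts with the intention-to-treat and CONSORT commitments for any randomised participant who leaves the study, most clearly for one whose week-8 score has already been collected. This is a stated rule that contradicts the stated analysis, not a detail left to a fuller document.

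The number affected, the direction and the size of any bias cannot be determined from the article. Under the assumed rates and correlations above, spurious differences run from 0 to about 0.15 SD; these are illustrations. It would be too strong to say that the rule defeats the intention-to-treat analysis as a whole: that is true for those removed, and if few or none decline the effect is small. The correction is still worth making promptly, because removed data cannot be recovered.

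**What to change.** Reconcile Withdrawal, Safety monitoring and reporting, and Statistical analysis by stating that:

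1. Stopping treatment is not the same as declining participation and does not trigger removal of data.
2. Data collected before withdrawal from the study are kept and analysed by randomised group, unless the participant explicitly asks for erasure.
3. The number and timing of erasures are reported by arm, with a de-identified count of everyone randomised.

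The cost is wording and an ethics amendment; no extra data collection follows from keeping what has already been given. There is one real constraint. The article reports that written consent had been obtained from all participants and that recruitment had closed (Methods/design; Trial status), so new wording cannot simply be applied to people already enrolled. For them, retention is subject to the consent they gave and to the data-protection law, and neither can be judged from this document. Where retention is not permitted, report removals by arm and describe the analysis as excluding those participants, rather than as intention-to-treat without qualification.
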